### Outcomes

The clinical outcomes in this study include the following adverse events experienced by patients during their inpatient stay:

Admission: A hospital admission following an ED visit [37-39]. Each ED attendance is classified as admission or discharge according to the clinical decision made. As a result, patients who left before a decision could be made are excluded rather than considered discharged.Inpatient death: A clinically certified death of a patient admitted to the hospital and who died during the hospitalization.2/7/30-day mortality: A clinically certified death of an admitted patient that occurred 2/7/30 days after the ED visit regardless of the place of death.ICU transfer: Identified using the hospital’s admission, transfer, and discharge database. Whenever a patient had more than one transfer from ward to ICU, only the data before the first transfer were included.Cardiac arrest: Defined as the loss of a palpable pulse with attempted resuscitation in the ward.Prolonged hospital length of stay: Defined as 21 days or more for the hospital stay.

**Table 1 table1:** List of the high-level constructed variables in the master data set, along with their sources and categories.

Category	Subcategory	Source table	High-level variables extracted

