### Data Source and Extraction

Study subjects have been drawn from the hospital’s EHRs using the SingHealth-IHiS Electronic Health Intelligence System, which combines data from multiple clinical, operational, and finance data sources [33]. Before analysis, all data, including the 3 primary identifiers, have been de-identified to ensure that they are sufficiently anonymous. Records of deaths are obtained from the national death registry and are matched to specific patients in our database. Relevant variables are extracted from the beginning of the ED visits until the end of the patient’s journey. Moreover, patients’ medical histories are extracted and matched for each unique patient through *“Patient ID.”* The extracted data were saved in multiple CSV files for subsequent processing and analysis.

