### Predictive Modelling for Clinical Decision Making

In this study, we will develop and validate a novel interpretable triage system for risk stratification of patients in the ED. Our proposed solution will be compared with baseline risk prediction tools such as traditional clinical scores and black box machine learning models. The extracted data set will be split into training, validation, and testing sets to build and validate the predictive models. The ED visit episodes from January 1, 2008, to December 31, 2018, will be randomly divided into 2 non-overlapping cohorts: a training cohort (80%) and a validation cohort (20%). The ED visits dated in 2019 are assigned to one testing cohort, while those dated in 2020 are assigned to a second testing cohort covering the period of the COVID-19 pandemic [40,41]. Using this sequential testing design, we will be able to test whether the population shift and the COVID-19 pandemic would impact model performance [42]. Further details are presented below.

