#### Proposed Method: Interpretable SERT

SERT consists of 3 scoring algorithms, each tailored to its application at different time points in the ED. On arrival at the triage station, SERT-1 is used to estimate patients’ likelihood of admission (inpatient and ICU) and 2-day mortality. SERT-1 is intended to assess the patient’s immediate urgency based on basic patient information, simple vital measurements, and medical histories readily available during triage. While in the ED, SERT-2 predicts patients’ admission (inpatient and ICU) and 2/7-day mortality using a variety of variables, including laboratory test results, vital signs, ED treatment, diagnosis, and some administrative information. As an extension of the SERT-1 algorithm, SERT-2 incorporates additional variables obtained during ED stay to better predict outcomes. On admission, SERT-3 predicts the likelihood of 7/30-day mortality, ICU transfer, and prolonged length of stay using variables collected in the ED and during the first 24 hours of inpatient stay. In actual clinical implementation, in the case where a patient has incomplete information, SERT will use imputation methods to fill in the missing values before calculating the risk score. In summary, SERT allows for a comprehensive risk assessment and prediction in the ED in a dynamic manner.

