## Results

The raw data have been extracted, and we are currently linking and cleaning the data. In the data extraction process, we included all patients who visited the ED at Singapore General Hospital between January 1, 2008, and December 31, 2020. Patients under the age of 21 years were excluded. If the patients were admitted through the corresponding ED visit, they would be followed throughout their inpatient stay. The data set contains more than 1.8 million ED visit episodes of over 810,000 unique patients. Approximately 650,000 of these ED visits resulted in subsequent hospitalizations. Our findings and modelling results are expected to be published by 2022.

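### SERT-1 is scored on arrival, but its admission performance is tested only on arrivals who stayed for a decision, and deaths after leaving are not counted

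*Protocol article*

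**What the plan says.** All references are to the protocol article.

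- **Outcomes, admission item.** Each attendance is labelled as admission or discharge from the clinical decision. It follows that "patients who left before a decision could be made are excluded rather than considered discharged".
- **Outcomes, mortality item.** The 2/7/30-day outcome is "A clinically certified death of an admitted patient that occurred 2/7/30 days after the ED visit regardless of the place of death".
- **Proposed Method: Interpretable SERT.** "On arrival at the triage station, SERT-1 is used to estimate patients’ likelihood of admission (inpatient and ICU) and 2-day mortality". Its inputs are "based on basic patient information, simple vital measurements, and medical histories readily available during triage". SERT-2, used during the ED stay, predicts admission and 2-day and 7-day mortality.
- **Data Source and Extraction.** "Records of deaths are obtained from the national death registry and are matched to specific patients in our database".
- **Predictive Modelling for Clinical Decision Making.** "The ED visits dated in 2019 are assigned to one testing cohort, while those dated in 2020 are assigned to a second testing cohort". This section does not mention patients who left.
- **Results.** At extraction, "we included all patients who visited the ED at Singapore General Hospital between January 1, 2008, and December 31, 2020", with under-21s removed. "The data set contains more than 1.8 million ED visit episodes of over 810,000 unique patients", and about 650,000 visits led to hospitalization.

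**The concern.** A triage score is used before the course of the visit is known. Removing visits because of something that happens later makes the test population differ from the population that will be scored. For SERT-1, the reported discrimination, predictive values and prevalence would describe arrivals who waited for a decision.

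For admission there is a reason to leave these visits out: no decision was made, so there is no label. For early mortality that reason does not exist, because registry death does not depend on how the ED visit ended. A patient who leaves undecided and dies within two days is a case that a triage score should be judged on, and under the present definitions that death cannot appear.

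The design also compares the 2019 and 2020 testing cohorts to detect population shift and a pandemic effect. If the share who left differed between those years, the two cohorts would be filtered differently. Without a count of leavers in each, a reader could not separate this from a change in model performance.

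**Working it through.** **Step 1. Timing.** SERT-1 is calculated at triage from triage information. Leaving before a decision comes afterwards. Exclusion on leaving is therefore selection on a post-triage event, and the mismatch for admission follows from the text alone.

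**Step 2. Mortality under two readings.**
- *Narrow reading:* the exclusion governs only the admission label. Leavers may stay in the mortality cohort, but they are not admitted patients, so their deaths do not meet the definition.
- *Broad reading:* leavers are removed from every analysis. Their deaths are absent because the patients are absent.

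Either way, deaths after leaving are lost, although the registry match could supply them.

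**Step 3. Size for admission.** The article states no leaving rate and no figure that can be reproduced, so this is a sensitivity calculation. The inputs are V = 1,800,000 visits and A = 650,000 admissions (Results), and an **assumed** leaving share L of 1%, 3% or 8%. V describes all extracted visits, so A/V = 650,000/1,800,000 = 36.1% is the all-visit rate, with leavers counted as not admitted.

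- Visits dropped = V × L.
- Admission prevalence with leavers dropped = A / (V × (1 − L)).
- Leavers' share of non-admitted visits: w = L / (1 − A/V) = L / 0.639.
- AUC over all arrivals = (1 − w) × AUC(admitted vs discharged) + w × AUC(admitted vs left). The shift is therefore w times the difference between the two AUCs. A difference of 0.10 is **assumed** for illustration.

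| L (assumed) | Visits dropped | Prevalence, leavers dropped | w | AUC shift at a 0.10 difference |
|---|---|---|---|---|
| 1% | 18,000 | 650,000/1,782,000 = 36.5% | 1.6% | 0.002 |
| 3% | 54,000 | 650,000/1,746,000 = 37.2% | 4.7% | 0.005 |
| 8% | 144,000 | 650,000/1,656,000 = 39.3% | 12.5% | 0.013 |

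**Step 4. Direction for PPV.** With leavers coded as not admitted, restoring them can add false positives but no true positives. At a fixed threshold, PPV is then equal or lower. The direction of the AUC shift is not determined.

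**Step 5. Size for 2-day mortality.** Let r be leavers' 2-day death risk relative to other arrivals (**assumed**). Their share of all 2-day deaths among arrivals is L·r / (L·r + 1 − L). At r = 1 this is 1%, 3% or 8%. At r = 0.5 it is 0.5%, 1.5% or 4.2% (for 8%: 0.04/0.96).

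**The case against.** The strongest defence is that the exclusion is a labelling rule. It sits inside the admission item, follows from the sentence on classifying attendances, and contrasts exclusion with being called discharged. Some leavers might have been admitted had they stayed, so declining to code them is reasonable. This stands: the exclusion can remain primary for admission. It does not remove the mismatch for a score calculated on arrival.

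A second defence is that the admitted-only mortality definition does more harm than the exclusion, since it also omits deaths in the ED and deaths after ED discharge. This also stands, and it means that keeping leavers in the cohort restores no deaths unless that definition is changed too.

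Three stronger readings are tempting, but the document does not support them:

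- *That Outcomes and Results contradict each other on the cohort.* The Results sentence describes the extraction step, and linking and cleaning were still under way. Extracting everyone and later excluding unlabelled visits for one outcome is an ordinary sequence.
- *That leavers are certainly removed from every outcome.* The sentence's position in the admission item leaves its scope open.
- *That the bias is concentrated in crowded periods and works through SERT-1's own inputs.* The article says nothing about when patients leave. Table 1 places consultation waiting time in the ED disposition group and does not list patient load among the triage variables.

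**Conclusion.** The point holds in a limited form. SERT-1's admission performance will be tested on arrivals who stayed for a decision, while the score is meant for use on arrival. Deaths after leaving cannot count towards early mortality on either reading of the exclusion, although the registry match makes them ascertainable.

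The size is unknown because the leaving rate is not given. Over the assumed 1% to 8%, prevalence in the analysed set rises by about 0.4 to 3.1 percentage points above 36.1%, and the AUC moves by roughly 0.002 to 0.013 if the 0.10 difference applies. That is probably modest. The statement that PPV cannot be higher for all arrivals rests on coding leavers as not admitted and on a fixed threshold. An effect on the 2019 versus 2020 comparison arises only if the leaving share differed between the years, which the document does not show.

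**What to change.** 1. State in the Outcomes section that the exclusion of patients who left undecided applies to the admission outcome only.
2. Keep leavers in the SERT-1 and SERT-2 cohorts for 2-day and 7-day mortality, and word that outcome as registry death within the stated number of days after the ED visit, whether or not the patient was admitted. Both changes are needed, since neither restores these deaths alone. SERT-3 is used on admission, so its mortality outcomes need not change.
3. For admission, keep the exclusion as the primary analysis. Add one sensitivity analysis in each testing cohort with leavers coded as not admitted, at the same threshold as the primary analysis.
4. Report the number and percentage of leavers in the 2019 and 2020 cohorts.

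The cost is a wording change to two outcome items and one extra run per testing cohort, on data that appear to be already extracted. PPV in the added analysis will be equal or slightly lower.

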**Information collected at ED disposition**			
	ED vital signs	ED vital signs	Vital measurement frequency and major ED vital readings: pulse, respiration, fraction of inspired oxygen, SpO_2_, systolic BP, diastolic BP, temperature, pain level scale, Glasgow coma scale, alert (extracted from physical notes)
	ED laboratory	ED laboratory	Laboratory measurement frequency and major laboratory test results: potassium, creatinine, sodium, bicarbonate, albumin, creatine kinase-MB (mass), creatine kinase, prothrombin time, N-terminal pro–B-type natriuretic peptide, C-reactive protein
	ED consultation and treatment	ED consultation, ED treatment	Services provider, consultation waiting time, ED location, length of consultation, resuscitation, major emergency surgeries, pre-selected major ordering
	ED allergy	ED allergy	Major allergy types and reasons, severity
	ED disposition and diagnosis	ED disposition, ED diagnosis	Disposition type, major primary diagnosis, secondary diagnosis (eg, trauma)
	Outcomes	ED disposition, ED root table	Admissions, mortality within ED, direct transfer to ICU

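### The 2/7/30-day mortality outcome counts admitted patients only, but SERT-1 and SERT-2 use it as a target before admission is known

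*Protocol article*

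**What the plan says.** All references are to the protocol article.

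- **Outcomes.** The list opens with "The clinical outcomes in this study include the following adverse events experienced by patients during their inpatient stay". Within it, 2/7/30-day mortality is "A clinically certified death of an admitted patient that occurred 2/7/30 days after the ED visit regardless of the place of death". The same list sorts each attendance into admission or discharge, and excludes patients who left before a decision.
- **Proposed Method: Interpretable SERT.** "On arrival at the triage station, SERT-1 is used to estimate patients’ likelihood of admission (inpatient and ICU) and 2-day mortality". For the second score: "While in the ED, SERT-2 predicts patients’ admission (inpatient and ICU) and 2/7-day mortality using a variety of variables". SERT-3 is used on admission and covers 7- and 30-day mortality.
- **Table 1, information collected at ED disposition.** The row labelled as outcomes lists "Admissions, mortality within ED, direct transfer to ICU".
- **Data Source and Extraction.** "Records of deaths are obtained from the national death registry and are matched to specific patients in our database".
- **Results.** All ED visitors from 2008 to 2020 were extracted, except those under 21: more than 1.8 million visits. "Approximately 650,000 of these ED visits resulted in subsequent hospitalizations".
- **Discussion, Strengths.** Mortality prediction is described there as serving patients who go on to be hospitalized.

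**The concern.** A score calculated at triage or during the ED stay is applied to everyone present, and nobody yet knows who will be admitted. The mortality outcome assigned to SERT-1 and SERT-2 exists only for those who are later admitted. Two kinds of early death then fall outside it: deaths in the ED, and deaths within 2 or 7 days of being sent home. These are events a triage score most needs to detect.

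The Significance section of the Discussion suggests that low-risk patients may need less intensive monitoring, and the performance section promises sensitivity and negative predictive value. Those figures mean what a reader will take them to mean only if deaths among patients judged low risk and discharged are counted. The comparison with PACS and the early warning scores would rest on the same labels.

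**Working it through.** The plan states no death rate, event count or sample size for this outcome, so there is no figure of its own to reproduce. The check compares passages and then does simple arithmetic on the visit counts.

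**Step 1: who can have the event.** The definition names an admitted patient. Its closing words about the place of death widen where the death may occur, not whose death counts. A patient who dies in the ED before admission, or at home after ED discharge, does not meet it.

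**Step 2: who is scored.** SERT-1 and SERT-2 both predict admission. A model for admission needs visits that did and did not end in admission, so the population of these two scores must include non-admitted patients. The extraction in Results agrees: all adult ED visits were taken. SERT-3 is used on admission, so for it definition and population match.

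**Step 3: the two ways to follow the text for SERT-1 and SERT-2.**

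- *Non-admitted visits are dropped from the mortality models.* The cohort is then selected on a decision made after the score is used, and that decision is another target of the same score. Sensitivity and negative predictive value describe the admitted, not the arrivals.
- *Non-admitted visits are kept.* Their deaths are then labelled as survival. A low score followed by death at home counts as a true negative, and a high score followed by death in the ED counts as a false positive. These errors push accuracy in opposite directions, so the net direction cannot be read from the document.

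The article does not say which applies.

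**Step 4: deaths in the ED.** Table 1 lists them as an outcome. The Outcomes section does not define them, its admission-or-discharge classification has no class for them, and no SERT score is assigned them.

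**Step 5: visits that cannot carry the event.** Inputs from Results: more than 1.8 million visits, about 650,000 hospitalizations.

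- Not admitted: 1,800,000 − 650,000 = 1,150,000.
- Share: 1,150,000 / 1,800,000 = 63.9%.

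This includes an unstated number who left before a decision.

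**Step 6: share of 2-day deaths missed (illustration only).** With assumed 2-day mortality *a* in admitted and *n* in non-admitted visits, the share is 1,150,000·*n* / (650,000·*a* + 1,150,000·*n*). Two sets of assumed rates:

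| *a* | *n* | Deaths missed | Deaths counted | Share missed |
|---|---|---|---|---|
| 1.0% | 0.02% | 230 | 6,500 | 230 / 6,730 = 3.4% |
| 0.3% | 0.10% | 1,150 | 1,950 | 1,150 / 3,100 = 37.1% |
| 2.0% | 0.05% | 575 | 13,000 | 575 / 13,575 = 4.2% |
| 0.5% | 0.20% | 2,300 | 3,250 | 2,300 / 5,550 = 41.4% |

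The first two rows are the extremes of one set of assumptions, the last two of another. The result is set by the assumed rates and shows only that the share could be small or large.

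**The case against.** The best defence is that the restriction is deliberate. The lead sentence of Outcomes speaks of the inpatient stay, the mortality definition names admitted patients, and Strengths describes mortality prediction for those who will be hospitalized. These three places agree, and mortality among the hospitalized is a legitimate target. This explains the definition and makes the dropped reading the likelier one. It does not remove the mismatch, because at triage and in the ED nobody can pick out the patients who will be hospitalized.

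A second defence is that a journal article may leave the analysis population of each score to the full protocol. That would excuse silence. Here the article states a definition, and the definition conflicts with the stated use.

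Three stronger readings are tempting, and the document does not support them:

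- A reader might infer that the plan codes non-admitted deaths as survival and so teaches the score that the most critical arrivals are low risk. No sentence says these visits are kept as non-events. Even if they were, deaths of admitted patients would still count, so risk would be biased and not necessarily reversed.
- A reader might infer that SERT-1 and SERT-2 are invalid as a whole. Their admission targets cover every attendance with a decision and are unaffected.
- A reader might infer that 64% of visits have a wrong mortality label. Under the highest non-admitted rate assumed above, 0.2%, at least 99.8% of those visits are true survivors. The 64% is the share that cannot carry the event, not the share mislabelled.

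**Conclusion.** The point holds for the mortality component of SERT-1 and SERT-2, and only there. The admitted-only definition does not fit scores used before admission is known, and both ways of following it bias the accuracy measures for ED arrivals. Deaths in the ED are named as an outcome in Table 1 but are neither defined nor assigned to a score.

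The size that rests on the document is about 1.15 million of 1.8 million visits (64%) unable to carry the event. The number and share of deaths missed, and the direction of the effect on accuracy, cannot be derived from it. The conclusion does not depend on the assumed rates. It needs only that some patients die in the ED or soon after ED discharge.

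**What to change.** For SERT-1 and SERT-2, define 2- and 7-day mortality as death from any cause, in any place, within 2 or 7 days of the ED visit, for every eligible ED visit. Count deaths in the ED and after ED discharge as events, using the linked death registry. State the analysis population of each score, including whether the exclusion of patients who left before a decision also applies to the mortality models. Keep the admitted-only definition for SERT-3. Align the lead sentence of Outcomes and the sentence in Strengths with the new definition.

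The cost is a reworded outcome and recoding of data already extracted. Results reports that linking and cleaning are still under way, and no new data source is needed. If mortality among the hospitalized is also of interest at triage, it can be reported as an additional, clearly labelled analysis.

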**Patient history**			
	Health care utilization summary	Inpatient movement, ED^a^ root table	Count of ED visits, emergency admissions, surgeries, ICU^b^ or HDU^c^ transfer in the patient’s history (past 30/90/180/365 days)
	Comorbidities	Diagnosis history	Charlson Comorbidity Index (17 variables; chronic disease), Elixhauser Comorbidity Index (30 variables)

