### Strengths

First, this study uses a large set of EHR data over a 13-year period, which contains comprehensive patient information. As Singapore’s largest hospital, Singapore General Hospital provides medical care to a wide range of patients throughout the country; thus, its EHRs ensure good coverage for a large population. Additionally, the longitudinal data allow us to validate the SERT system using data before and after COVID-19. Thus, we will have the opportunity to evaluate the impact of the global pandemic on triage performance in the ED. The insights gained from system evaluation could be used to examine possible model adaptations in shifted clinical settings.

Second, the SERT triaging system we intend to develop will be transparent and easily understandable. All 3 SERT scores are parsimonious and point-based, as only the most significant variables are considered in their formulation. Their formats follow the same convention as widely used clinical scores such as the National Early Warning Score and Modified Early Warning Score, allowing for easy comprehension and quick adoption. In contrast, black box machine learning models are challenging to comprehend, making them inaccessible to clinicians [25]. Although there are techniques for post hoc model explanation, most machine learning models are not inherently interpretable [25].

Third, this project aims to develop a dynamic system capable of identifying risk strata at different decision points in the ED. During the initial triage process and the patient’s stay in the ED, SERT predicts the likelihood of inpatient and ICU admissions. Whenever variables are altered, the scores can be updated, making the risk assessment dynamic and practical. In addition, SERT can make mortality predictions to assess the likelihood of the worst outcomes for patients who will be hospitalized.

Lastly, the simple form of the scores in SERT permits a variety of implementation schemes. As an example, the actual implementation can be as simple as a mobile app. Users may input relevant information into the app, which will return a risk score at the time of inquiry. The SERT scoring platform can also be easily integrated into existing information technology systems, which requires only simple calculations and therefore little computing power. The application can be designed and implemented in real time, similar to that seen in a recent study in the United States [13].

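### On the stated dates, the 365-day utilization counts are left-truncated for 2008 visits (about 9% of the development data) but complete in the 2019 and 2020 test cohorts

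*Protocol article*

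**What the plan says.** The Patient history block of Table 1 defines the utilization predictors as counts in the patient's "history (past 30/90/180/365 days"), built from the inpatient movement and ED root tables. The same block takes the Charlson and Elixhauser variables from a diagnosis history table and gives no look-back length for them.

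The Results section says that extraction "included all patients who visited the ED at Singapore General Hospital between January 1, 2008, and December 31, 2020". Under Predictive Modelling for Clinical Decision Making, "The ED visit episodes from January 1, 2008, to December 31, 2018, will be randomly divided into 2 non-overlapping cohorts", namely "a training cohort (80%) and a validation cohort (20"%). The testing cohorts follow in time: "The ED visits dated in 2019 are assigned to one testing cohort, while those dated in 2020 are assigned to a second testing cohort". The Strengths section says "this study uses a large set of EHR data over a 13-year period".

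Data Source and Extraction adds that medical histories are extracted and linked by patient identifier. It does not say how far back they go. The article describes no lead-in period and no exclusion of early visits.

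**The concern.** The first visit eligible for training falls on the first day of the extracted ED visits. A count over the past 365 days for a January 2008 visit can then draw on a few weeks of records at most, and the window fills only by the end of 2008. In the testing cohorts the same variable always has its full window. A predictor with one name would be measured differently in part of the development data and in the test data.

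Two things are at stake. First, AutoScore ranks variables, sets cut-offs and assigns points from the development data. Undercounting history in some of those visits tends to weaken the 365-day variables relative to others. Second, the sequential testing design is meant to show whether population shift affects performance. A difference in record length adds a small artefact to the development-versus-test comparison. The random 20% validation cohort comes from the same years and carries the same share of truncated visits, so it cannot reveal the problem.

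**Working it through.** **Inputs from the article.** ED visits extracted January 1, 2008 to December 31, 2020 (Results). Development period January 1, 2008 to December 31, 2018, split 80/20; testing in 2019 and in 2020 (Predictive Modelling). Windows of 30, 90, 180 and 365 days (Table 1). More than 1.8 million visits (Results). More than 120,000 visits a year (Study Setting).

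**Assumptions.** Visits are spread evenly over time, and no history records precede January 1, 2008.

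**The stated span.** January 1, 2008 to December 31, 2020 is 4,749 days, and 4,749 / 365.25 = 13.00 years. The 13 years in the Strengths section equal the visit window, with nothing left over for a lead-in.

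**Share of development visits with an incomplete window.** The development period has 4,018 days. Number the days d = 0, 1, 2, … from January 1, 2008. A window of w days is incomplete when d < w, so the affected share is w / 4,018.

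| Window | Affected share of development |
|---|---|
| 365 days | 365 / 4,018 = 9.1% |
| 180 days | 180 / 4,018 = 4.5% |
| 90 days | 90 / 4,018 = 2.2% |
| 30 days | 30 / 4,018 = 0.7% |

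**How much of the 365-day window is seen.** Coverage on day d is min(d, 365) / 365.
- Over the 366 days of 2008 this sums to (365 × 366 / 2) / 365 = 183, so mean coverage is 183 / 366 = 50%.
- The other 3,652 development days have full coverage, so the mean over development is (183 + 3,652) / 4,018 = 0.954, about 95%.

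**Test cohorts.** January 1, 2019 has 4,018 earlier days of data and January 1, 2020 has 4,383. Both exceed 365, so no test visit has a truncated 365-day window within this hospital's records.

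**Number of visits.** 1,800,000 / 4,749 = 379 visits a day.
- Affected: 379.03 × 365 ≈ 138,000 development visits, of which 80% (about 111,000) are in training and 20% (about 28,000) in validation.
- At 120,000 visits a year, the affected number is about 120,000.

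**Sensitivity to even spread.** If 2008 volume was r times the average of the other development years, the affected share is 365r / (366r + 3,652). For r = 0.7 this is 6.5%; for r = 1 it is 9.1%.

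**If development starts on January 1, 2009.** 3,652 of 4,018 days remain (90.9%), or 379.03 × 3,652 ≈ 1.38 million of about 1.52 million visits. The earliest has 366 days of prior data, so every 365-day window is complete.

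**The case against.** The strongest reply is that truncation is inferred. The Results dates describe the ED visits that bring patients into the study. Histories are described as a separate extraction linked by patient, and the 13-year figure is a summary statement under Strengths. Older records in the inpatient movement or diagnosis history tables cannot be ruled out. This stands for counts drawn from inpatient movement, where truncation is likely but not established. It is weaker for prior ED visits, because extraction of ED visits is itself dated from January 1, 2008.

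It can also be said that a condensed article need not give table start dates or look-back definitions. That is fair for the comorbidity variables. It does not dispose of the utilization counts, where the stated window and the stated dates do not fit together.

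The effect is also small: half the window is still seen on average in 2008, and the 30-day count is barely touched. This stands in full.

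Four stronger readings are tempting but not supported:
- **Frequent attenders in 2008 are coded as having no history.** That is close to true only in the first weeks of the year.
- **All three SERT scores are affected.** The article names medical histories for SERT-1, and SERT-2 extends it. SERT-3 is described through ED and first-24-hour variables. AutoScore keeps a sparse subset, so no history variable is certain to enter any score.
- **The pandemic comparison is distorted.** For these counts, 2019 and 2020 both have complete windows.
- **Recorded comorbidity is inflated by a known amount in the test cohorts.** This needs a diagnosis history that starts in 2008, use of all prior records, and a rate of first recording. The article gives none of these.

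**Conclusion.** The point holds in a limited form. On the stated dates, 365-day utilization counts are left-truncated for visits in 2008 and complete in both test cohorts. With even visit numbers, 9.1% of development visits are affected (6.5% if 2008 volume was 70% of the other years' average), or about 120,000 to 138,000 visits. The case is firm for prior ED visits and a likely inference for inpatient-movement counts.

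The consequence is modest: some weakening of the 365-day history variables in development and a small record-length artefact between development and testing. It does not touch the 2019-versus-2020 contrast in these counts. For comorbidities only a conditional statement is justified: if the diagnosis history also begins in 2008 and all prior records are used, capture will rise with calendar time.

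**What to change.** State the first date of each history table. If records from at least January 1, 2007 were extracted, giving that date settles the utilization counts, and no visits need be dropped.

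Otherwise, use 2008 only as a look-back year and start the training/validation cohort on January 1, 2009. At minimum, refit without 2008 visits as a sensitivity analysis and report whether variable ranking, points and test performance change.

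Define one comorbidity look-back that is the same for every visit. Its length is for the investigators to choose, since a shorter window records fewer chronic conditions.

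The main change is a date filter, and the Results section says the data are still being linked and cleaned. The cost is about 9% of development visits, leaving roughly 1.38 million. The sensitivity analysis costs one further model fit per score and loses no visits from the main analysis.
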